#### Medication dosage errors

Errors in drug dose administration (domain) in milligrams will be measured on video reviewing (specific measurement) both as the percentage and absolute deviations from the 2018 AHA PALS cardiac arrest algorithm (metric). Errors will be also measured both as the percentage deviation from the amount of delivered drug compared with the correct weight dose as prescribed by the physician and the absolute deviations from that dose (metric). For the second scenario, errors in fluid resuscitation volumes (in milliliters) will be measured as a deviation from the 2018 ATLS guidelines (metric). An initial 20 mL/kg bolus of isotonic crystalloid followed by 10–20 mL/kg of packed red blood cells and 10–20 mL/kg of fresh frozen plasma and platelets are expected [40]. Moreover, defibrillations (in Joules) and the number of shocks will be also measured during the first scenario (metric) [50]. Mean error rates will be aggregated to compare both study arms (method of aggregation). The time frame of interest for this endpoint is over the duration of the whole CPR scenario.

#### System usability scale (SUS)

At the end of each evaluation, we will measure the participants’ perceived usability (domain) of InterFACE using the system usability scale (SUS) questionnaire (specific measurement) designed by Brooke [53]. It consists of a 10-item questionnaire with five response options for each item (metric), based on their level of agreement ranging from 1 (strongly disagree) to 5 (strongly agree). Following Brooke’s scoring system, for odd-numbered statements 1, 3, 5, 7, 9 (positively-worded items), the score contribution is equal to the scale position minus 1 (e.g., strongly agree: 5–1 = 4). For even-numbered statements 2, 4, 6, 8, 10 (negatively-worded items), the score contribution is equal to 5 minus the scale position (e.g., strongly agree: 5–5 = 0). Each score contribution will fall within the range of 0 to 4. The participant’s scores for each item are then added up together and multiplied by 2.5 to convert the original scores of 0–40 to 0–100. Although the scores are 0–100, these are not percentages of usability and should be considered only in terms of their percentile ranking. To obtain a SUS score of 100, the respondent must answer five to all odd questions and 0 to all even questions. It is generally considered that a score of 75 and above is good, while a score of 50 and 75 is fair. A score below 50 reveals strong disagreement in terms of satisfaction. The mean SUS score in the intervention group will be used to assess the overall perceived usability of InterFACE (method of aggregation). The time frame of interest for this endpoint is over the duration of the whole CPR scenario.

#### Perceived stress and satisfaction

A three-item questionnaire using a 10-point Likert scale will be administered to participants (specific measurement). It will measure: (1) the stress perceived before the scenario starts (“on a scale from 1 to 10, how stressed are you now?”); (2) the overall stress perceived at the end of the scenario (“on a scale of 1 to 10, how stressed (maximum reached) were you during the drug preparation period?”); and (3) the satisfaction about the tools used during the resuscitation scenario (“on a scale of 1 to 10, how satisfied were you with your preparation experience?”) (domains). The scales range from 0 (minimum score) to 10 (maximum score), increments are integers between 0 to 10 (metric). For stress, higher values represent a worse score, whereas for satisfaction higher values represent a better score. No subscales will be combined. Stress and satisfaction scores will be expressed as percentages in conjunction with absolute n/N values. Mean scores will be aggregated to compare both study arms (method of aggregation). The time frame of interest for this endpoint is over the duration of the whole CPR scenario.

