**Assessments**					
**Demographic data**			X		
**(T)SAGAT**				X	
**RTLE (leadership)**					X
**TEAM (teamwork, communication)**					X
**Time to 2nd outcomes**				X	
**Medication/defibrillation errors**				X	
**3-item termination questionnaire (10-point Likert scale)**					X
**SUS questionnaire**					X

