### Intervention and resuscitation scenarios

Each team will comprise six participants: (1) a team leader (fellow in pediatric emergency medicine), (2) a physician (resident in pediatrics) undertaking the primary/secondary surveys and performing the procedures, (3) a dedicated trained assistant for airway management, (4) a dedicated trained assistant for chest compressions, (5) a nurse for vascular access and drug preparation/administration, and (6) a scribe (second nurse) to document events and actions in a chronological fashion (either with the app or conventional methods). As PALS instructors and senior physicians, the study investigators will not interfere in the conduct of the CPR (except in the case of a significant deviation from the algorithm that must be followed to achieve ROSC; which will then be regarded as an error). Among them, a study investigator will play the role of on-call hospital specialists and radiologists, if needed. A second study investigator will operate the simulator and a third will freeze the situation at certain defined timepoints and provide the scripted questions.

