A first rater (one of the study investigators) will review all videos. To assess the reproducibility of the video review procedure, a second reviewer will independently duplicate the review in a random sample of 20% of all videos. Interrater reliability scores on video reviewing will be calculated using Cohen’s kappa coefficient for categorical variables. We define poor reliability as a kappa coefficient of < 0.4, fair reliability as 0.4–0.6, good reliability as > 0.6–0.8, and excellent as > 0.8. Any disagreements in video reviewing will be resolved by a third independent investigator, including appropriate revision of the implemented reviewing strategy, followed by double-reviewing of a further 10% until reliability on video reviewing (a kappa of 0.6 or greater) is achieved. For continuous variables, the Bland-Altman method will be used to plot the difference of values reported by both reviewers against the mean value for each outcome. The limits of agreement will be assessed by the interval of ± 1.96 SDs of the measurement difference on either side of the mean difference. The null hypothesis that there is no difference on average between both reviewers will be tested using a *t* test. The mean difference will be reported with its 95% CI. Additionally, the intraclass correlation coefficients for the volumes of drugs drawn, time to drug preparation, and time to drug delivery will be assessed, assuming that raters are a sample from a larger population of possible raters.

Finally, means and SDs will be determined for perceived stress and satisfaction scores of participants for each scenario, as well as for the SUS questionnaire, and reported with descriptive statistics. In the case of missing data, a complete case analysis will be conducted. No multiple imputations are planned. All statistical tests will be two-sided with a type I error risk of 5%. Data analysis will be performed using GraphPad Prism, version 7 (GraphPad Software, San Diego, CA, USA) for graph figures, and R version 4.0.4 (R Foundation, Vienna, Austria) for descriptive statistics and statistical tests.

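### Stress and satisfaction items 2 and 3 do not ask about their stated domains, the response range is given two ways, and Table 1 schedules no pre-scenario rating

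*Protocol article*

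**What the plan says.** The section Perceived stress and satisfaction gives, for each of three items, the domain and then the scripted question.

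- **Item 1.** The domain is stress before the scenario. The question asks, in the present tense, how stressed the respondent is at that moment.
- **Item 2.** The domain is "the overall stress perceived at the end of the scenario". The question is "how stressed (maximum reached) were you during the drug preparation period".
- **Item 3.** The domain is "the satisfaction about the tools used during the resuscitation scenario". The question is "how satisfied were you with your preparation experience".

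The time frame for the endpoint is the whole CPR scenario. All three scripted questions offer a scale from 1 to 10, but the metric then reads "The scales range from 0 (minimum score) to 10 (maximum score"), in whole-number steps. The questionnaire goes to participants without restriction by role.

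Table 1 has one row for the instrument, "3-item termination questionnaire (10-point Likert scale"), with a single X under Close-out. Intervention and resuscitation scenarios lists six roles per team, of which the fifth is "a nurse for vascular access and drug preparation/administration". Statistical analyses states that "means and SDs will be determined for perceived stress and satisfaction scores of participants for each scenario", as descriptive statistics.

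**The concern.** For items 2 and 3 the domain and the question stand side by side and differ. Stress over a scenario is not the same quantity as peak stress during one task within it, and satisfaction with a tool is not the same as satisfaction with a preparation experience. InterFACE is a display meant to support the whole team. An item tied to drug preparation misses most of the exposure that it should evaluate.

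The schedule adds a second problem. If the trial is run from Table 1, the question about stress at this moment is answered after both scenarios, and the pre-scenario rating does not exist. It could not be obtained later, because Data collection and management describes a single 60-minute observation per team with no follow-up.

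**Working it through.** The check is mainly a comparison of statements, with a few counts.

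**1. Domain against question (Perceived stress and satisfaction)**

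| Item | Domain | What the question asks | Match? |
|---|---|---|---|
| 1 | Stress before the scenario | Stress now | Yes, if asked beforehand |
| 2 | Overall stress, whole scenario | Maximum stress, drug preparation period | No: period and summary both differ |
| 3 | Satisfaction with the tools used | Satisfaction with a preparation experience | No: no tool is named and the object is unclear |

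Item 2 departs from its domain twice: the scenario becomes one period within it, and overall stress becomes the maximum. Item 3 does not say which preparation is meant. Coming straight after item 2 it suggests drug preparation, but it does not say so.

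**2. Who is assigned drug preparation**

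Inputs: six roles per team, one of which prepares drugs (Intervention and resuscitation scenarios); 8 teams and 48 participants (Power and sample size calculation).

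- Assigned preparers: 8 × 1 = 8, and 8/48 = 16.7%.
- Other participants: 48 − 8 = 40, and 40/48 = 83.3%.

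These figures count assigned roles. They do not count valid and invalid answers.

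**3. Response range**

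- 1 to 10: 10 − 1 + 1 = 10 levels, which agrees with a 10-point scale.
- 0 to 10: 10 − 0 + 1 = 11 levels, which does not.

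A rating of 1 is the lowest possible answer on the first scale and one step above the lowest on the second.

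**4. Schedule against text**

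- Table 1: one administration, at close-out.
- Item 1: needs an answer before the scenario.
- Statistical analyses: needs scores for each of two scenarios.

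Three items for each of two scenarios come to 2 × 3 = 6 answers per participant. One close-out form with three items yields 3. Items 2 and 3 could be asked retrospectively for each scenario on a longer close-out form. Item 1 could not, because its question refers to the present moment.

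**The case against.** The strongest reply is that the consequences are easily overstated. Several parts of it stand.

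**Validity of the answers.** A reader might infer from the role count that stress and satisfaction are valid for only 8 respondents. The document does not support that. Item 1 does not mention drug preparation. Item 2 names a period, and a leader or a compressor can rate their own stress during it. Item 3 does not contain the word drug. The drug process also involves others: a physician prescribes (Medication dosage errors), the app calculates weight-based doses (The InterFACE tool), and the scribe documents, with the app in one arm. The fault in item 2 is a window too narrow for its domain, not 40 invalid answers.

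**Item 1 and Table 1.** The wording of item 1 suits its domain, and Outcome measures calls Table 1 schematic. The single row may be shorthand for an instrument given at two times. That reading is plausible, but the row is labelled as a termination questionnaire and marked only at close-out, so the table and the text still conflict.

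**Comparison or description.** A reader might also see a contradiction between the outcome section, which compares arms, and Statistical analyses, which plans descriptive statistics. Means and SDs by arm are a descriptive comparison, and the outcome section promises no test. Nor does the text call for a baseline-adjusted, clustered model: with 8 teams, 4 per arm, that would be a preference, not the repair of an error.

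**Disclosure.** The Discussion admits that the questionnaire has not been validated. That covers missing psychometric work. It does not cover questions that differ from their own domains, and the same paragraph still relies on the questionnaire to measure differences in stress and satisfaction.

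**Conclusion.** The point holds as an internal inconsistency in one secondary instrument, in three parts.

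- Items 2 and 3 do not ask about their stated domains or match the whole-scenario time frame. Item 2 is plainly wrong on both period and summary; item 3 is at best ambiguous. Item 2 centres on a task assigned to 8 of 48 participants, although the other 40 can answer it.
- The response range is stated as both 1 to 10 and 0 to 10.
- Table 1 conflicts with item 1 and does not fit reporting by scenario. The loss of the pre-scenario rating follows only if Table 1 is applied literally.

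The role count assumes that drug preparation stays with the role it is assigned to. The SAGAT primary analysis, the sample size and the other secondary outcomes are unaffected. The correction is worth making because the text as written would collect answers to questions other than those to be reported.

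**What to change.** - Reword item 2 to ask about overall stress during the resuscitation scenario, and item 3 to ask about satisfaction with the tools used during it.
- Choose one response range and state it identically in the items and the metric.
- Split the Table 1 row so that item 1 is asked before each scenario and items 2 and 3 after it.
- Keep any questions between scenarios out of the 10-minute rest, which the protocol reserves as free of cognitive load. Items 2 and 3 for the first scenario can be asked before the rest begins, and item 1 for the second scenario after it ends.

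The cost is an edit to a three-item form and one table row, plus 6 − 3 = 3 extra answers per participant compared with a single close-out form. The descriptive analysis can stay as planned. If answers have already been collected on the present form, the report should give the exact wording, response range and time of administration, and should label the outcomes by what was asked.

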### Data collection and management

Data collection will be carried out by the responsive simulator detectors (Laerdal SimBaby) and the two GoPro video cameras. The set-up of both cameras will be standardized to record at a resolution of 1080p at 60 frames per second, a wide field of view, and a 16:9 aspect ratio. Similarly, the position of the cameras will be standardized. The first camera will be placed over the manikin’s head, below the LCD screen, to allow to capture footage of the whole resuscitation scene. The second camera will be placed on a tripod, 2 m away from the manikin’s feet, where the leader will stand to film the scene from the leader’s point of view (including a view on the patient monitor). The recorded videos will be safely stored in duplicate on secured hard-disk drives in a locked room at the Geneva University Hospitals. As all scenarios will be fully video-recorded, all actions, communications, and interactions will be later scored by two raters to allow for the calculation of interrater reliability. The length of the freezes will be measured using the video recordings and deducted from the whole scenario duration to allow accurate measure of the different timed outcomes. All actions performed with the app will be automatically saved locally in log files for further analysis. This study offers the major advantage to observe a unique 60-min period per resuscitation team. Therefore, neither follow-up nor retention plans will be necessary. The resuscitation algorithm is highly standardized and deviation from the algorithm is a parameter of interest in our study. Data collection will be carried out using the REDCap database (REDCap, Vanderbilt University, Nashville, TN, USA; https://www.project-redcap.org/resources/citations/) by trained investigators.

### Power and sample size calculation

A previous study found a 23.5% SA improvement in intensive care unit nurses exposed to an integrated information display compared to a traditional display exposure [54]. In this trial, the sample size was calculated to provide 90% power at a two-sided alpha level of 5% in detecting a relative difference of at least 25% SA improvement between intervention groups, with an assumed standard deviation (SD) set at 0.2. This SD is based on and conservatively about twice as much as that observed by Koch et al. [54]. The required sample size is 14 participants per study arm. To prevent a potential loss of power due to misspecification of assumptions, 18 participants (= 3 teams of 6 people per team) should be recruited per randomized group. To take into account the cluster randomized trial design, this sample size was inflated using a variation inflation factor of 1.25 (= 1 + 0.05(6–1); 0.05 being the intraclass correlation coefficient). The total sample size (i.e., 45 participants) was finally rounded up to 48 participants to obtain 8 teams of 6 participants per team.

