### Primary outcome

#### Situational awareness

Direct measures of SA through the SA global assessment technique (SAGAT) instrument were found to be a highly sensitive, reliable, and predictive measure of individual and team performance in a patient-simulated environment [21]. In this trial, SAGAT questionnaires representing the three SA levels (i.e., perception, comprehension, and projection) were adapted from Coolen et al. [19] by an expert panel of senior pediatric emergency physicians, nurses, and a statistician using a goal-directed task analysis (GDTA) methodology as described by Endsley et al. [46] (Additional file 2). SA (domain) expressed as a score in absolute value in conjunction with percentage (metric) will be measured using the SAGAT (specific measurement) during video review of each scenario. Both the individual participant SAGAT score and the team SAGAT score, defined as the degree to which each team member possesses the SA required for their role and calculated as the sum of individual SAGAT scores, will be calculated [42, 47]. The SAGAT scores will be further divided into their three dimensions to individually evaluate perception, comprehension, and projection of each team member and to compare them to what truly happened during the simulation. This will be done similarly for the TSAGAT. According to Endlsey et al. [46], the SAGAT responses for categorical variables will be scored as either correct (1) or incorrect (0) by two of the investigators. For numerical responses, answers will be considered correct based upon a 10% pre-defined tolerance range settled by the research investigators around the true value. Higher SA scores will denote higher SA. Mean overall scores will be aggregated to compare both study arms (method of aggregation). The time frame of interest for this endpoint is over the duration of the whole CPR scenario.

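### The 14 per arm comes from an absolute difference of 0.25, but the target is stated as a 25% relative gain, so 90% power is not shown for the stated effect

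*Protocol article*

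**What the plan says.** All the inputs are in the protocol article under Power and sample size calculation. Power is 90% at a two-sided 5% level. The target is "detecting a relative difference of at least 25% SA improvement between intervention groups, with an assumed standard deviation (SD) set at 0.2". The SD is described as "conservatively about twice as much as that observed by" an earlier study of intensive care nurses, which is also cited for a 23.5% improvement in SA. The result is "The required sample size is 14 participants per study arm". This is raised to 18 per arm (three teams of six) as a margin against wrong assumptions, multiplied by 1.25 for clustering to give 45 in total, and rounded to 48, which is eight teams of six.

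The section does not give the unit of the SD, an expected control-arm mean, or whether the earlier 23.5% was relative or in percentage points. Under Primary outcome, Situational awareness, the score is "expressed as a score in absolute value in conjunction with percentage", with a possible range of 0 to 16 on each questionnaire. The score is therefore bounded above.

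**The concern.** A relative difference turns into a difference in score units only through the control mean: difference = 0.25 × control mean. The section never makes that conversion, yet it divides a 25% effect by an SD given as a plain number. If the 25% went in directly as 0.25, the calculation answers a different and easier question from the one in the text, because on a 0–1 score 25% of any attainable control mean is less than 0.25.

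This is the only power justification for the primary endpoint. If SA does not differ significantly between the arms, a reader would take the section to mean that a 25% relative gain would have been found nine times in ten. On the natural reading of the stated inputs, that assurance has not been established.

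**Working it through.** **Inputs from the protocol article.** Two-sided alpha 5% (z = 1.960); power 90% (z = 1.282); SD 0.2; effect 25%; 24 per arm in the final design (48 ÷ 2); design effect 1 + 0.05 × (6 − 1) = 1.25.

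**Assumptions.** The SD of 0.2 is on the score as a 0–1 fraction (it would be implausibly small on a 0–16 or 0–100 scale). The control mean is not given, so 0.5 to 0.8 is used. The upper end is fixed by the scale: a 25% relative gain must not pass 1.00, so the control mean can be at most 1 ÷ 1.25 = 0.80.

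**Step 1: reproduce the plan's figure.** n per arm = 2 × (1.960 + 1.282)² × (SD ÷ difference)². With a difference of 0.25: 2 × 10.51 × (0.2 ÷ 0.25)² = 2 × 10.51 × 0.64 = 13.45, rounded up to 14. The later steps also reproduce: 2 × 18 × 1.25 = 45, then 48.

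Other readings do not give 14 by this formula: one-sided alpha gives 11, 80% power gives 11, a difference of 0.235 gives 16, and log(1.25) with SD 0.2 gives 17. A result of 14 needs a difference between about 0.245 and 0.254. If that is 25% of a control mean, the control mean is at least 0.245 ÷ 0.25 = 0.98, which leaves no room for a 25% gain.

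**Step 2: use the effect as stated.** Difference = 0.25 × control mean. Power of the final design = Φ(difference ÷ 0.2 × √(19.2 ÷ 2) − 1.960), where 19.2 = 24 ÷ 1.25 is the effective number per arm and √9.6 = 3.098.

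| Assumed control mean | Difference | n per arm for 90%, before inflation | Power with 48 participants |
|---|---|---|---|
| 0.8 | 0.200 | 22 | Φ(3.098 − 1.960) = 87% |
| 0.7 | 0.175 | 28 | Φ(2.711 − 1.960) = 77% |
| 0.6 | 0.150 | 38 | Φ(2.324 − 1.960) = 64% |
| 0.5 | 0.125 | 54 | Φ(1.936 − 1.960) = 49% |

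**Step 3: what 48 participants detect with 90% power.** Difference = 0.2 × √(2 ÷ 19.2) × 3.242 = 0.209. For that to be a 25% relative gain, the control mean would be 0.209 ÷ 0.25 = 0.837 and the intervention mean 1.25 × 0.837 = 1.046, above the maximum score. So with SD 0.2 on the 0–1 score and one score per participant, no feasible control mean reaches 90%.

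**Step 4: the absolute target.** For a true difference of 0.25, the same method gives Φ(1.25 × 3.098 − 1.960) = 97%. The planned size is consistent with an absolute target; the mismatch is with the word relative.

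**The case against.** The strongest defence is that 0.2 is in the same relative unit as the target, that is, the SD divided by the control mean. Then 0.2 ÷ 0.25 is a ratio of two relative quantities, the control mean cancels, and 14 is right as worded. The text does not say this: it names an SD and derives it from one observed in an earlier study. The document does not give the scale of that earlier SD, however, so the defence cannot be excluded, only called unsupported. Even if it is what was meant, the section still needs a correction, since it names a different quantity.

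A second defence is that relative is a slip for percentage points. If so, the sample size and the 90% both stand and only one word is wrong. This is quite possible, and the fix below allows for it.

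Third, the power figures above may be pessimistic. Each participant completes two scenarios, and the calculation uses one score. If 0.2 is the SD of a single scenario's score and the two scores correlate at 0.5 (an assumption, with the design effect kept at 1.25), the SD of a participant's average is 0.2 × √0.75 = 0.173, and power becomes 95%, 88%, 77% and 61% at control means of 0.8, 0.7, 0.6 and 0.5. The protocol also calls its SD conservative; at half of it, 0.1, power is at least 97% across the same range. Both points stand. They do not rescue a claim made at SD 0.2 by a calculation that neither uses the second score nor states a within-person correlation, but they limit what can be concluded.

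A reader might infer that the trial cannot detect a 25% relative gain, or that it must recruit more teams. The documents support neither: the true SD may be smaller, the second score may add precision, and the control mean is unknown. A reader might also add the loss of power from having only eight teams. That loss is separate; it would be present with a true absolute difference of 0.25 as well, and it is not counted here.

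**Conclusion.** The point holds in limited form. The stated 14 per arm corresponds to an absolute difference of 0.25 with SD 0.2, not to a 25% relative improvement on a bounded score, so the 90% is not shown for the effect the section names. By the plan's own method the final 48 participants give 87% at the highest feasible control mean (0.80) and 77% to 49% at 0.7 to 0.5.

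The direction of the error does not depend on which feasible control mean is assumed; its size does. Both rest on reading 0.2 as the SD of the 0–1 score, with one score per participant. The margin from 14 to 18 and the rounding to 24 per arm are already included; they narrow the gap without closing it.

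**What to change.** In the sample size section, state the scale of the SD. Then choose one of two wordings:

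- **Absolute target.** Restate the effect as a difference of 25 percentage points of queries answered correctly (0.25 × 16 = 4 points on the 0–16 score), with an SD of 20 percentage points (0.2 × 16 = 3.2 points). The 14 then follows as printed. The effect is feasible only if the control mean is at most 0.75, and it is a larger effect than the present wording suggests.
- **Relative target.** Keep the 25% relative improvement, state the assumed control mean, and replace 90% with the power that results. If the two scenarios per participant are to be credited, state the within-person correlation used.

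If 0.2 was meant as the SD divided by the control mean, say so and give its basis; the 14 then stands.

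The change is to wording only and needs no extra participants. The cost is a less favourable stated target or a lower stated power.
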